### 4.5. Validity and Reliability/Rigor

To ensure adherence to the protocol and that the data are collected in the same way by the different professionals, it will be compulsory to take an accredited training course with theoretical and practical content in order to join the Clinical Care Group, with all information being provided in writing. In addition, the facilities in the intervention group will receive specific and accredited training on the health education intervention.

Additionally, the NIC taxonomy [34] will be used to standardize the interventions that will be implemented and unify the steps to be taken by professionals. Furthermore, recruitment will be blinded for the participating professionals to avoid selection bias in the different groups, and randomization will take place once the informed consent of all participants has been obtained.

It is also important to note the rationale for using a cluster or parallel cluster randomized clinical trial (RCT) design. Cluster RCTs are considered the most suitable designs for validating interventions that will be implemented at the organizational rather than individual level [35]. Moreover, the implementation of clusters for each facility would avoid potential “contamination” between patients receiving the health education intervention and those in the control group by reducing the dilution bias of the intervention effect [36] and improving the rigor and consistency of each of the study groups.

A number of strategies have been used in the study design to avoid or reduce potential biases associated with the cluster design such as the possibility of unbalanced groups in terms of magnitude, unequal attrition rates between groups, and selection bias in different groups. These strategies include ensuring that the groups are balanced in terms of: magnitude before the end of the recruitment period; recruiting patients, taking attrition rates into consideration in both groups; applying the same inclusion and exclusion criteria to both groups; and training research professionals to ensure that informed consent and data collection are obtained in the same way from both groups.

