### 2.5. Recruitment of Facilities and Professionals

For recruitment purposes, researchers will contact PCFs and clinicians via an email sent by a scientific society of primary care nurses. Professionals interested in participating will be interviewed by the principal investigator.

Participating facilities shall have at least three nurse collaborators who will be able to deliver the proposed health educational intervention, as well as a suitable room available in the same basic healthcare district in which to implement the intervention in case they are assigned to the intervention group.

Participating professionals will become members of the FEARFALL_CARE Clinical Care Group. Each nurse will be recruiting approximately five participants. If a PCF is assigned to the control group, professionals will perform recruitment, study assessment interviews, and clinical practice as usual. If a PCF is assigned to the intervention group, at least three nurses shall participate in the recruitment and assessment interviews and at least two nurses will implement the educational group intervention (with one delivering the session and the other acting as an observer).

Finally, to minimize the risk of selection bias, PCF professionals shall recruit participants without the knowledge of the group to which they will be assigned.

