#### 2.6.3. Withdrawal Criteria

Any participant who, after the beginning of this study, experiences events that may cause them to meet any of the exclusion criteria or to be in breach of the inclusion criteria shall be withdrawn from the trial. The data of the terminated subject will be collected until such time as non-compliance with the eligibility criteria is identified. No patients will be replaced, as the established sample size includes an additional 20% of participants to accommodate for potential losses.

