### 2.7. Sample Size

We expect to be able to recruit ten PCFs (five assigned to the intervention group and five to the control group). Assuming a significance level of 0.05, a difference of 3.8 points on the Short Falls Efficacy Scale-International (FES-I), a standard deviation of 5.1 points, and an intraclass correlation coefficient of 0.1, at least 12 participants will be required per center (a total of 120 participants) to reach a power of 80%. Allowing for a loss of 20%, the necessary sample size will be 150 individuals (75 patients assigned to the intervention group and 75 to the control group; approximately 15 patients in each PCF, about five patients per nurse).

Patients seen by nurses at each participating facility and meeting the eligibility criteria will be recruited using a consecutive sampling method until the required sample size—which will be the same for all participating facilities—has been reached.

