### 4.3. Visit Plan

During the study period, both study groups will make the following visits (see Table 2):-Initial visit: screening.-Pre-intervention baseline visit: Collection of data on variables. Approximate duration: 60–80 min. The patients assigned to the control group shall carry it out up to two weeks before the beginning of the initial health education intervention.-Five initial sessions with the intervention group.-Visit post initial intervention (visit window: ±4–8 weeks after randomization (for the control group) or ±2 weeks after the initial sessions (for the intervention group)): Collection of data on variables. Approximate duration: 25 min.-Visit at six months post initial intervention (visit window: ±2–4 weeks, at six months after randomization (for the control group) or after the initial health education intervention (for the intervention group)), always prior to the booster session. Collection of data on variables. The structured education plan proposed in the Portfolio of Services will be reviewed in both groups, as well as in the patients in the intervention group, including a follow-up of the issues identified during the health education intervention. Approximate duration: 45 min.-Booster session with the intervention group.-Visit at 12 months (visit window: ±2–4 weeks, at 12 months post randomization in the control group or at 6 months after the booster session in the intervention group). Collection of data on variables. Approximate duration: 20 min.

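### The order of consent, baseline assessment and allocation is stated inconsistently, so the baseline short FES-I may be taken after the arm is known

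*Protocol article*

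**What the plan says.** All references are to the protocol article.

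**Text that puts allocation after recruitment.** Section 4.5 states that "randomization will take place once the informed consent of all participants has been obtained". Section 2.5 states that "PCF professionals shall recruit participants without the knowledge of the group to which they will be assigned", and section 2.9 says that blinding is possible only during recruitment. Section 2.6.3 adds "No patients will be replaced", because the sample size already carries a 20% allowance.

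**Text that presupposes an allocation.** Section 4.5 lists, as measures against unequal arm sizes and unequal attrition, "ensuring that the groups are balanced in terms of: magnitude before the end of the recruitment period" and "recruiting patients, taking attrition rates into consideration in both groups". Section 2.5 sets out what staff do once their facility has an arm, and recruitment is among those tasks in both arms. Section 4.3 says of the baseline visit: "The patients assigned to the control group shall carry it out up to two weeks before the beginning of the initial health education intervention". Table 2 ticks informed consent at screening and again at baseline. Its first footnote gives the two-week baseline window to the intervention group, whereas section 4.3 gives it to the control group.

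**Text that is silent.** Section 2.8 has the allocations placed in sealed envelopes. It does not say when they are opened relative to the baseline visit.

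**The concern.** If randomisation follows everyone's consent, there are no arms and no arm-level attrition while recruitment is open. A measure phrased in terms of the groups before recruitment ends does not fit that order when read literally. The wording in sections 2.5 and 4.3 and in Table 2 points the same way, so the reader cannot tell whether recruitment, consent or baseline assessment may fall after allocation.

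The baseline measurement is the most exposed part. The trial is open, and the nurses who recruit also carry out the assessment interviews (section 2.5). Section 4.4 describes effectiveness as the decrease in the short FES-I. If a participant answers the baseline questionnaire, or a nurse administers it, knowing that a group course will or will not follow, the starting point of that decrease is no longer protected by randomisation. Blinded recruitment before allocation is the trial's main safeguard here, and it cannot be restored afterwards.

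**Working it through.** **1. Does the plan need recruitment adjusted by arm to reach its figures?**

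Inputs from section 2.7: alpha 0.05, target difference 3.8 on the short FES-I, SD 5.1, ICC 0.1, 12 participants per centre in 10 centres, 80% power and 20% loss. Five facilities per arm comes from sections 2.7 and 2.8. A two-sided test is assumed, since sidedness is not stated.

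- Individually randomised size per arm: 2 × [5.1 × (1.960 + 0.842) / 3.8]² = 28.28.
- Design effect at 12 per centre: 1 + (12 − 1) × 0.1 = 2.1.
- Clustered size per arm: 28.28 × 2.1 = 59.4, so 60 = 5 × 12 per arm and 120 in total. Power at 12 per centre is 80.4%.
- With 20% loss: 120 / 0.80 = 150, that is 75 per arm and 15 per facility.

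The plan's figures reproduce. Section 2.7 fixes the same quota for every facility, so any draw of five facilities gives 5 × 15 = 75. A 20% loss leaves 15 × 0.80 = 12 per facility, the number required. Arm sizes are therefore balanced with nobody knowing the allocation.

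Unequal attrition with the same average loss (assumed splits, normal approximation) barely moves power:

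- 20% in both arms: 80.4%.
- 10% in one arm and 30% in the other: 80.1%.
- 0% in one arm and 40% in the other: 79.3%.

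These figures use a normal approximation. A t reference with 8 degrees of freedom gives about 69% at 12 per centre, but that is a separate matter and does not bear on this point.

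**2. What order do the sections give?**

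- *Consent.* Section 4.5 puts everyone's consent before randomisation. Table 2 ticks it at screening, which fits, and again at baseline, with no reason given.
- *Recruitment.* The closing sentence of section 2.5 has it done blind. The paragraph before lists it among the duties of a facility that already has an arm.
- *Baseline visit.* Section 4.3 and Table 2 tie it to the start of the education sessions, not to randomisation, and disagree on which arm the two-week window covers. Control facilities hold no sessions, so the start date of the sessions is not an event in that arm.
- *Training.* Section 2.10 trains intervention staff separately, as a group already assigned. That training must fall between allocation and the first session. If baseline must lie within two weeks of that session, it can easily fall after allocation.
- *Short FES-I.* A score of 11 or more is an entry criterion (section 2.6.1), and eligibility is reviewed at screening. Table 2, however, records the outcome measurement first at the baseline visit. No section places that measurement before the envelopes are opened.

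**3. How would a post-allocation baseline enter the result?**

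Decrease = baseline − follow-up. If knowledge of the arm shifts the mean baseline response in one arm by b and leaves follow-up unchanged, that arm's mean decrease shifts by b, and so does the between-arm difference in decrease. If follow-up scores alone are compared, b does not enter. The documents give no basis for a value of b.

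**The case against.** The strongest defence is that section 4.5 describes design features fixed in advance. It says the strategies were used in designing the study and lists them beside common eligibility criteria and uniform training. The equal quota, five facilities per arm, the 20% allowance and the no-replacement rule achieve size balance and allow for losses without unblinding anyone. The references to assigned facilities and patients may simply label them by the arm they will eventually have. A second consent tick does not show that anyone first consents after randomisation. The article also condenses a fuller protocol.

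Most of this stands. A reader might infer that recruitment is to be steered by arm size and arm attrition, with nurses who know the allocation adding selected patients to the smaller arm. The documents do not support that. They describe no monitoring of enrolment by arm, no topping up and no enrolment after allocation, and section 2.6.3 rules out replacement. The selection bias that would follow from such a practice is therefore conditional on something not planned.

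Two things remain. A uniform 20% allowance protects the total number but does nothing about attrition that differs between arms, which is the bias the sentence claims to address. The defence also does not explain the disagreement over the baseline window, or place the baseline short FES-I before allocation. These are statements in conflict, not detail left to a fuller document.

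**Conclusion.** The point holds as an inconsistency in the stated order of consent, baseline assessment and allocation, with one practical consequence: as written, the baseline primary outcome may be collected after participants and nurses know the arm. The documents do not show that this will happen; they fail to exclude it.

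No sample size or power figure changes. The possible bias cannot be sized from the documents. It matters to the extent that the analysis uses the decrease from baseline, as section 4.4 describes, and that knowledge of the arm affects baseline answers. It is a cheap improvement worth making before recruitment closes, not a demonstrated flaw in procedure.

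**What to change.** 1. In section 4.5, replace the two arm-level strategies with a statement that balance in size comes from the equal quota per facility, and that losses are covered by the 20% allowance fixed in advance. Do not present that allowance as a remedy for attrition that differs between arms.
2. In sections 2.8 and 4.5, state that consent and the baseline short FES-I are completed for all participants before the allocation envelopes are opened, and that nobody is enrolled afterwards.
3. In section 2.5, move recruitment out of the duties listed by assigned arm, so that it agrees with the blinding rule that closes the section.
4. In section 4.3 and Table 2, reword the baseline visit so that it does not refer to patients already assigned, and explain or remove the second consent tick. Reconcile the two-week window between the text and the footnote, and check it against the new order, since completing every baseline before allocation may not fit within it.

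The cost is a change of wording and a longer interval between baseline and first session at facilities that fill early. Sample size and recruitment targets stay as they are.

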### 4.6. Clinical Risk Management

Clinical risk management has been considered to ensure the safety of participants in all phases of this study. Health education interventions to reduce fear of falling in older people at the community level have shown positive results in various studies [16,17,18,19,20,21,22,23,24]. For this study, those with evidence support have been selected, which is a guarantee of quality.

To ensure that no subjects with unfavorable conditions participate in this type of intervention at the community level and that no situations arise that create a risk to the health of the participants, measures will be taken at different stages of this study [37]:-Screening and pre-selection visits will allow the assessment of the baseline physical and mental condition of the participants, which will ensure whether they can safely participate in the multicomponent exercise program. Inclusion criteria include that participants must be independent for activities of daily living or with mild functional dependence, independent for walking, and not present cognitive impairment (details are given in the inclusion and exclusion criteria section).-The intervention visit will be carried out by nurses specifically trained in the field of primary care to implement the program, who will monitor the performance of the activities and ensure their adaptation to the functional capacities of each individual. Homogeneous training of the professionals involved in this study will ensure the safe implementation of the intervention.-Follow-up visits will allow close monitoring of each participant to monitor and detect possible conditions that pose a risk to health.-If during the intervention/follow-up a change in the patient’s clinical condition is detected that is a criterion for withdrawal, to ensure patient safety, the patient will not continue in this study. In addition, the patient will be followed up either in primary care or, if necessary, in specialized care.

In addition, this study has been approved by the Ethics Committee of the Gregorio Marañón Hospital and the Central Research Committee of the Primary Care Management of Madrid that guarantee the application of good research practices in the field of primary care. This study is considered a low-intervention clinical trial, in which the additional burden on the safety of the subjects is minimal compared to that of normal clinical practice and does not require coverage by an insurance contract [38].

Finally, this study is carried out on subjects covered by the National Health System, specifically in Spain, health coverage includes access to common services that guarantee adequate, comprehensive and continuous health care for all users, including public health services, primary care, specialized care, emergency care, pharmaceutical care, orthoprosthetic care, dietary products and medical transport [39].

Therefore, in the case of this type of study (a low-intervention clinical trial), immediate risk management will be covered and guaranteed by the National Health System healthcare for all participants.

## 5. Expected Results

The purpose of this study is to explore the possibility of improving FOF and the incidence of falls in community-dwelling people over 65 years of age through a group educational intervention carried out by nurses. This is the first study conducted in Spain, with the main objective of reducing FOF through nursing interventions in the primary care setting. This study will measure the effectiveness of the health education intervention at 1, 6 and 12 months, which means that the effect of the health education intervention will be assessed both in the short and long term.

This study protocol attempts to unify effective interventions into a single educational group intervention that could be implemented in a standardized way in the primary care setting. After a review of the relevant literature on effective interventions for this type of patient, we believe that a single intervention focusing on functional ability enhancement, fall prevention, cognitive restructuring, ability to cope, and anxiety management could represent the priority type of intervention for these patients, as reported in previous publications on the topic [3,4,9,18,19,21,22,24,35,40,41].

Moreover, the multicenter approach of this study and the data collected on these variables will help to assess the feasibility of incorporating the health education intervention into daily clinical practice.

If the health educational intervention proves effective, it could be of great value to patients living with this prevalent health problem, as it would facilitate the screening of FOF and the application of this type of intervention in nurses’ offices, thus helping to reduce long-term disability caused by voluntary activity restriction at earlier stages of life. Furthermore, the results of this study may contribute to future research aimed at addressing these issues among community-dwelling individuals over 65 years of age.

It is also our belief that the 12-month follow-up described above may yield valuable data for future studies in this line of research, as the duration of clinical trials in this line of research is usually no longer than 6 months [17,42,43]. In addition, it is important to know whether the effect of the group-based educational intervention has a long-term impact on patients, contribute providing long-term evidence on effective health education interventions to reduce fear of falling and falls in older people living in the community. Finally, this study could be added to other studies with results after 12 months, evaluating the sum of long-term research, also encouraging long-term research.

### Limitations

This study features a number of drawbacks. Firstly, a selection bias may be introduced during recruitment at PCFs. The recruitment of participants who are visiting their healthcare professionals could influence the results. However, it is not possible to recruit them randomly using databases, as there are no registers of patients with FOF. Secondly, given the nature of this study, the health education intervention cannot be blinded to participants. Thirdly, the validity of the data to be extracted from health records could be underestimated in cases with poor documentation. Finally, participants will be recruited only in the Autonomous Community of Madrid due to financial and human resources constraints, which may limit the generalizability of the results.

Difficulties may also be encountered when implementing this study, as it is an health education interventional trial with four scheduled visits, in which attrition rates may be high due to dropouts, non-attendance, or non-compliance with instructions. To mitigate this problem, we aim to maximize patient retention through regular telephone calls, in which appointments will be arranged with participants prior to each interview. Furthermore, an additional 20% of participants will be recruited to accommodate for potential losses.

## 6. Conclusions

Once this study is completed, it will be possible to assess the effectiveness of the proposed health education intervention in improving FOF and the incidence of falls in the older population.

A 12-month follow-up may provide valuable information on the sustained impact of such interventions, which could serve as a basis for future research, encouraging the adoption of longer evaluation periods.

If the health education intervention is shown to be successful, it shall be recommended that the entire procedure be widely integrated into routine practice in primary care settings.

## Figures and Tables

**Figure 1 healthcare-12-02510-f001:**
[figure not shown]
CONSORT flowchart of participants.

**Table 1 healthcare-12-02510-t001:** Short FES-I scale.

Short FES-I Scale How Concerned Are You About the Possibility of Falling While…?	Not at All Concerned	Somewhat Concerned	Fairly Concerned	Very Concerned
1. Getting dressed or undressed	1 □	2 □	3 □	4 □
2. Taking a bath or shower	1 □	2 □	3 □	4 □
3. Getting in or out of a chair	1 □	2 □	3 □	4 □
4. Going up or down stairs	1 □	2 □	3 □	4 □
5. Reaching for something above your head or on the ground	1 □	2 □	3 □	4 □
6. Walking up or down a slope	1 □	2 □	3 □	4 □
7. Going out to a social event (e.g., religious service, family gathering or club meeting)	1 □	2 □	3 □	4 □
SUBTOTAL:	Add all the 1’s	Add all the 2’s	Add all the 3’s	Add all the 4’s
	Short FES-I ≥ 11: Fear of falling			

**Table 2 healthcare-12-02510-t002:** Summary of visits and variables.

Variables	Visits						
	Initial Visit. Screening	Pre-Intervention Baseline visit ^1^	Five Initial Group Sessions	Visit Post Initial Intervention ^2^	Visit at Six Months Post Initial Intervention ^3^	Booster Session	Visit at 12 Months ^4^
Review of eligibility criteria	x						
Informed consent	x	x					
Primary outcome variable: Short FES-I		x		x	x		x
Secondary outcome variable: Post intervention falls		x		x	x		x
EXPLANATORY VARIABLES							
Sociodemographic variables		x					
Functional variables		x			x		
Usual footwear		x			x		
Clinical variables		x					
Falls during intervention				x		x	
Ability to practice self-care		x		x	x		x
Perceived health and anxiety		x		x	x		x
Acceptability (among patients)				x			

^1^ ±2 weeks before the health education intervention (for the intervention group: (IG)). ^2^ ±2 weeks after the initial sessions (IG). ±4–8 weeks after randomization (for the control group (CG)). ^3^ ±2–4 weeks, at six months after randomization (CG) or after the initial health education intervention (IG), always prior to the booster session. ^4^ ±2–4 weeks, at 12 months post randomization (CG), at six months after the booster session (IG).

